### Data management {19}

All measures will be administered via online questionnaires at both pre- and post-test via www.soscisurvey.de [38]. This German server is ISO27001 certified and guarantees organisational, structural, and technical security in accordance with current standards. The server is accessed via SSH-encrypted connection. No data is passed on to third parties. No other person has access to the data, in accordance with section 11 of the Federal Data Protection Act. The server uses SSL encryption. Data is already encrypted on the participant’s browser and only decrypted on the server. No IP addresses are stored in the access log files and no cookies are used.

Due to questionnaires being administered online, missing values can be prohibited by not allowing to skip questions. Outcome data will be checked for unrealistic answer patterns (e.g. always the first option).

Outcome data will be stored on secure, password-protected platforms at the Karl Landsteiner University of Health Sciences. Only direct research associates can access the data.

### Confidentiality {27}

All data used in this study is anonymized. Email addresses will only be used to send out consent forms and links for the study but cannot be connected to the participants. Each participant will receive a unique identification number at the end of the pre-test questionnaires that they will use to log into the game and in all subsequent study parts. This code will be changed to one number for each participant for analysis as well as any data sharing.

### Plans for collection, laboratory evaluation, and storage of biological specimens for genetic or molecular analysis in this trial/future use {33}

Not applicable as this is neither an ancillary study nor includes the collection of biological specimens.

## Statistical methods

### Statistical methods for primary and secondary outcomes {20a}

#### Randomisation

To evaluate the randomisation process, baseline variables will be compared between experimental group and control group, first based on the intention-to-treat principle, which means that all participants are considered in the analyses regardless if they completed all questionnaires or not. Second, the baseline comparison will be repeated for the main analysis sample, which comprises all participants with completed questionnaires.

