### Sample size {14}

For the sample size calculation, we consider the percentage of adolescents with a positive change in iER skills between pre- and post-test. We assume that in the experimental group, the number of positive strategies improves by 30%, in the control group it improves by 10%. A chi-square test with a sample size of 62 adolescents per group will have 80% power (significance level 0.05). We expect approximately 30% drop-outs; thus, the total sample size is increased to 180. If in the control group only 1% improves compared to 21% in the experimental group, with this sample size the study has a power of more than 90%.

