#### Secondary analyses

*Emotion regulation and emotional competence*. For the two questionnaires about emotion regulation and emotional competence, comparisons between groups will be performed for the pre-test and for the change between pre- and post-test (items change in the Likert scale is set to + 1 or − 1 if the Likert scale improves or worsens, by one point, respectively, and so forth). For both analyses, a Wilcoxon test will be performed.

*Sex differences within the experimental group*. Adaptive iER strategies will be dichotomised into positive engagement vs acceptance and for each participant the more frequent strategy will be determined. Our outcome variable is the proportion of which sex uses positive engagement (or acceptance). A chi-square test will be calculated to compare the percentage between the sexes. Second, a logistic regression analysis will be performed to evaluate if gender stereotype scores have an influence on the more frequent strategy positive engagement or acceptance. Note that for this analysis only adolescents from the experimental group will be considered.

*Feasibility*. Data from the feasibility questionnaire will be analysed using descriptive statistics. Open questions will be analysed qualitatively following thematic analysis [48].

For the secondary and exploratory analyses, the significance level for all tests is set to 0.05, *p*-values are interpreted in a descriptive manner. The statistical software programs R and SPSS will be used [49, 50].

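### Between-arm baseline comparisons cannot show that randomisation worked, and among completers they are a weak way to detect selective drop-out

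*Protocol article*

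**What the plan says.** The Randomisation section of the protocol article, under {20a}, states a purpose and a comparison: "To evaluate the randomisation process, baseline variables will be compared between experimental group and control group". This is done first for everyone randomised. Then: "Second, the baseline comparison will be repeated for the main analysis sample, which comprises all participants with completed questionnaires". The section gives both comparisons the same purpose and names no test, threshold or decision rule.

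The Secondary analyses section, for EROS and ESCQ, says that "comparisons between groups will be performed for the pre-test and for the change between pre- and post-test" and then "For both analyses, a Wilcoxon test will be performed". It adds that "the significance level for all tests is set to 0.05" and, of the resulting p-values, that these "values are interpreted in a descriptive manner".

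Three other places matter:
- **Sequence generation {16a}:** the survey software allocates each child at the end of the pre-test questionnaires.
- **Sample size {14}:** "We expect approximately 30% drop-outs; thus, the total sample size is increased to 180".
- **Section {20c}:** drop-outs enter sensitivity analyses on the intention-to-treat principle, and nothing is imputed.

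**The concern.** The two samples raise different questions, but the plan treats them as one.

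In all randomised children, the baseline scores exist before the software allocates. If allocation ran as described, any between-arm difference is chance. A small p-value is then a false alarm, and a large one does not show that the process worked.

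In completers, a difference beyond chance is no longer about randomisation. It shows that different kinds of children left the two arms. That is a real possibility here, because one arm has an adventure game of about three hours that players aim to finish and the other a puzzle game played as much as the child likes. The main analysis sample is the completers, so selective loss could bias the primary chi-square test. The planned comparison looks for this indirectly, because the signal from the 30% who left is spread over the 70% who stayed.

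**Working it through.** **Inputs from the protocol.** Assumed rates: "We assume that in the experimental group, the number of positive strategies improves by 30%, in the control group it improves by 10"% (Sample size {14}). That section also gives 62 per group, 80% power, significance level 0.05, 30% drop-out and 180 in total. Allocation is 1:1 (Trial design {8}). Sidedness is not stated, so two-sided tests are used.

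**The plan's own figure.** With a pooled proportion of 0.20:

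n = [1.96·√(2·0.2·0.8) + 0.8416·√(0.3·0.7 + 0.1·0.9)]² / 0.2² = (1.1087 + 0.4610)² / 0.04 = 61.6, so 62 per group.

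Power at 62 is 80.3%. Allowing for drop-out, 124 / 0.70 = 177.1, or 178 when rounded up to an even number, against 180 stated. The figure reproduces. Of 180 randomised, 126 complete (63 per arm) and 54 drop out (27 per arm).

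**Power of a Wilcoxon test among completers.** The Wilcoxon test has efficiency 3/π relative to the t-test under normality. The effective n is 63 × 0.955 = 60.2 per arm, and the standard error of the shift is √(2/60.2) = 0.182 SD. Power is approximately Φ(d/0.182 − 1.96).

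| Baseline shift d | Power |
|---|---|
| 0.1 SD | 8% |
| 0.2 SD | 19% |
| 0.3 SD | 38% |
| 0.4 SD | 59% |
| 0.5 SD | 78% |

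Power of 50% needs d = 1.96 × 0.182 = 0.36 SD. Power of 80% needs (1.96 + 0.84) × 0.182 = 0.51 SD.

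**Selective drop-out in one arm (assumed).** The simulation has 90 children per arm, 30% loss in each, a normal baseline score and two-sided Wilcoxon tests at 0.05. Loss is random in the control arm. In the experimental arm the log-odds of leaving fall by 0.5, 0.75 or 1.0 per SD of baseline score, which means odds factors of 1.65, 2.1 and 2.7.

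| Log-odds per SD | Shift between completer arms | Between-arm completer test rejects | Completers vs drop-outs in that arm rejects |
|---|---|---|---|
| 0.5 | 0.14 SD | 12% | 54% |
| 0.75 | 0.20 SD | 20% | 85% |
| 1.0 | 0.25 SD | 29% | 97% |

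Repeat runs differ by at most 3 percentage points.

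**Other patterns (assumed).**
- If selection runs in opposite directions in the two arms, the completer test rejects in 25%, 57% and 88% of trials at odds factors of 1.5, 2 and 3 per SD.
- If selection is the same in both arms, it rejects in about 5%.
- In all randomised children it rejects in about 5% under selective drop-out in one arm, because drop-out cannot appear in that sample.

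**Precision of the within-arm comparison.** The standard error of a standardised difference is √(1/63 + 1/27) = 0.23, so the 95% interval is about ±1.96 × 0.23 = ±0.45 SD.

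**The case against.** The strongest reply is that the protocol never says what a non-significant result would mean. A reader might infer that non-significance will stand as evidence of balance, but no such rule is written, and the secondary p-values are to be read descriptively. The Randomisation section names no test and could describe an ordinary by-arm table. The Wilcoxon test belongs to the secondary analyses and is not tied to either sample. All of this stands, so the power figures show what the test would do among completers if it were used there.

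A reader might also conclude that the check misses most imbalance in general. That holds below about 0.36 SD and in the one-arm scenarios above. It does not hold for larger shifts or for opposite-direction selection at an odds factor of 2 or more. The protocol gives no drop-out pattern that would settle which applies.

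Nor is the completer comparison the only look at drop-out. Section {20c} and the feasibility paragraph of {18a} plan sensitivity analyses for drop-outs, and drop-out rates are examined after 40 participants. However, {20c} does not say how a child without a post-test enters an analysis of change when nothing is imputed.

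The two detection rates answer different questions. Completers against drop-outs shows whether leaving is related to baseline, not whether the retained arms differ. If selection is equal in both arms, they stay balanced on that variable and the between-arm test has no imbalance to find. The within-arm comparison therefore complements the between-arm table and does not replace it.

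Finally, a false-alarm rate of 1 − 0.95⁸ = 34% could be put on the pre-test tests, but it assumes eight independent scores. The protocol does not list the scores tested, and the ESCQ total depends on its subscales. With two independent tests the rate is 1 − 0.95² = 10%. No single figure is supported.

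**Conclusion.** The point holds in a limited form. The pre-test Wilcoxon test tells the reader nothing useful about randomisation in all randomised children. Among completers it would be weak for small to moderate shifts, with 19% power at 0.2 SD and 38% at 0.3 SD. Under the assumed one-arm drop-out, the pre-test data already collected are more sensitive to selective loss when completers are set against drop-outs (54% to 97%) than when the completer arms are compared (12% to 29%).

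These figures assume normal scores, two-sided tests, 30% loss in each arm and drop-out patterns that the protocol does not give. No planned analysis depends on the baseline comparison, so the primary chi-square test is the same whatever it shows. This is an inexpensive improvement to how comparability and drop-out are examined, and it does not show that the primary result would be wrong.

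**What to change.** 1. **Secondary analyses:** remove the between-arm Wilcoxon test of pre-test EROS and ESCQ. Keep the test of change.
2. **Randomisation:** report baseline variables by arm with standardised differences, in all randomised children and in completers. Draw no inference about the randomisation process.
3. **Drop-out:** report the rate by arm. Within each arm, compare pre-test values of completers and drop-outs using standardised differences with confidence intervals. Do not set a pass/fail limit such as 0.2 SD, because intervals of about ±0.45 SD could not show that it was met.
4. **Primary analysis:** add a supportive model of positive change adjusted for pre-specified baseline variables, at least the pre-test vignette count and language. The planned logistic regression does not serve this purpose. It includes language but not the pre-test count, and it also includes playtime, which arises after allocation.

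The cost is wording in two paragraphs, a small extra table and one extra model. The data are already collected before allocation. The drawback is the wide within-arm intervals, which rest on about 27 drop-outs per arm.

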#### Primary analysis—interpersonal emotion regulation skills

First, descriptive statistics will be generated for each observation time (pre- and post) and for each group: for continuous variables, mean and standard deviation (or median and interquartile range in case of a skewed distribution, respectively) and for categorical variables absolute and relative frequencies will be computed.

Answers of the vignette task will first be qualitatively assessed to exclude maladaptive as well as nonsensical strategies and merge answers that can be defined to be the same strategy. To analyse the main question, the change in the absolute number of positive strategies between pre- and post-test as well as the percentage of adolescents with a positive change in iER skills will be considered. A chi-square test (main analysis) will be calculated to compare the percentage between the two groups. Then, a logistic regression analysis will be performed for the dependent variable “positive change yes/no” to investigate the influence of the independent variables “time between last time of playtime and post-test”, “language”, “total playtime”, and “group”. To compare the change in absolute numbers, a non-parametric Wilcoxon rank-sum test will be performed (secondary analysis). The significance level will be set to 0.05.

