### Outcomes {12}

Our primary outcome in this study is the change of iER strategies participants can think of from pre (baseline)- to post-intervention, i.e. if the percentage of participants who improve their knowledge about possible iER strategies is higher in the experimental group compared to the control group. This is done via a vignette-task. The follow-up will be approximately 5 days after baseline measures.

In secondary analyses, we will test iER as a corroborating variable with a questionnaire. The questionnaire was not developed to measure change of iER skills over a short period of time (it asks for iER strategies use in the last 2 weeks) and is thus used as a complementary measure. As the game addresses general topics around emotions additionally to specific iER strategies, we will also examine the change in general emotional competence. Furthermore, effects of sex and gender on strategy choice and feasibility of the game will be examined.

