## Data collection and management

### Plans for assessment and collection of outcomes {18a}

#### Primary outcome—interpersonal emotion regulation

Vignettes [39] are used to depict short sequences of events and have been successfully used in psychological research (e.g. [40]). While often consisting of short written text, we will use visual vignettes [41] (to reduce reading for the participants and to be able to show emotional expressions) with hypothetical situations that require the use of iER before and after the game to assess if children’s perception of their options have changed, i.e. if they can think of more strategies to help a person in a hypothetical situation after they have played the iER AG. A visual scene will depict an every-day life situation with a person experiencing a negative emotion that needs to be regulated. Every participant will receive the same four different scenarios, containing 1 image depicting the scene (Table 3). For each scenario, participants get an open-ended question (“If you were in that room, what could you do in this situation to help this person? Write down everything you can think of.”).

**Table 3 Tab3:** Vignette task for interpersonal emotion regulation strategies

	Scenario	Emotion
1.	An early adolescent trips over in front of their peers.	Embarrassment
2.	An early adolescent is scared of a spider.	Fear
3.	An early adolescent is being excluded by their peers.	Sadness
4.	An early adolescent is angry because someone broke their phone.	Anger

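### The main test reduces strategy counts to any increase yes or no, and no analysis of the count, EROS or ESCQ adjusts for the pre-test value

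*Protocol article*

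**What the plan says.** Under Plans for assessment and collection of outcomes {18a}, the vignette task is open-ended: "Every participant will receive the same four different scenarios, containing 1 image depicting the scene", and the child lists every way of helping that comes to mind. After maladaptive and nonsensical answers are removed and duplicates merged, each child has one count before and one after play.

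Outcomes {12} describes the primary outcome as "the change of iER strategies participants can think of from pre (baseline)- to post-intervention" and then specifies it as a comparison of the percentage who improve. In the primary analysis section, "the percentage of adolescents with a positive change in iER skills will be considered" and "A chi-square test (main analysis) will be calculated to compare the percentage between the two groups". No minimum increase is set.

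Two further analyses follow. First, "a logistic regression analysis will be performed for the dependent variable" positive change yes/no, with time since last play, language, total playtime and group as independent variables. Second, "To compare the change in absolute numbers, a non-parametric Wilcoxon rank-sum test will be performed (secondary analysis". The pre-test count is a covariate in neither.

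Under Secondary analyses, EROS and ESCQ are compared between groups at pre-test and on the pre-post change, both by Wilcoxon test, again without a baseline covariate.

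**The concern.** Cutting the change at zero treats a gain of one strategy like a gain of ten, and no change like a loss of five. The Hypotheses section asks whether players recall more strategies than controls, which is a question about a number. If the game lifts that number broadly, the cut discards information the trial already holds.

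The second loss is separate. A change score subtracts the baseline but does not adjust for it. Because pre- and post-test counts are imperfectly correlated, change depends on the starting value, so a chance difference between groups at pre-test adds noise to the comparison. Randomisation takes place at the end of the pre-test questionnaires, so the covariate exists for every randomised child, including those who later drop out.

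At stake are power, and an effect estimate with an interval on the scale of the hypothesis. The validity of the test is not in question.

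**Working it through.** **1. The plan's own figure.** Inputs from Sample size {14}: 30% versus 10% improving (read as proportions of children), 80% power, alpha 0.05 (taken as two-sided).

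n per group = [1.960·√(2·0.20·0.80) + 0.842·√(0.30·0.70 + 0.10·0.90)]² / 0.20² = (1.109 + 0.461)² / 0.04 ≈ 61.6, so 62.

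This agrees with the statement "A chi-square test with a sample size of 62 adolescents per group will have 80% power (significance level 0.05". With 30% drop-out, 62/0.70 = 88.6, so 89 per group or 178 in total, close to the stated 180. The alternative of 21% versus 1% gives power 0.954 at 62 per group, which fits the claim of more than 90%. The arithmetic is right for the chosen test.

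**2. Cost of the yes/no cut at the planned rates.** Assume a normal change score with 10% and 30% of children above zero. The shift is z(0.90) − z(0.70) = 1.282 − 0.524 = 0.757 SD.

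Comparing the change itself: n = 2·(1.960 + 0.842)² / 0.757² ≈ 27.4, so 28 per group instead of 62. The cut costs 1 − 28/62 = 55% of the sample. If 30–50% of controls improve, the chi-square needs about 1.6 times the n, a loss of 1 − 1/1.6 ≈ 38%.

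**3. Further gain from baseline adjustment.** With equal variances and pre-post correlation ρ, ANCOVA residual variance relative to the change-score variance is (1 − ρ²) / [2(1 − ρ)] = (1 + ρ)/2.

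| ρ (assumed) | Variance ratio | n per group |
|---|---|---|
| 0.3 | 0.65 | 18 |
| 0.5 | 0.75 | 21 |
| 0.7 | 0.85 | 24 |

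**4. Simulated counts, whole-group shift.** Gamma-Poisson counts, 62 per group, 2,000 runs per setting, controls unchanged, game group mean 25% higher, between-child CV 0.4 or 0.7. All of these inputs except 62 are assumptions.

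| Baseline mean | Chi-square | Wilcoxon on change | ANCOVA |
|---|---|---|---|
| 4 | 0.34–0.35 | 0.43 | 0.52–0.57 |
| 8 | 0.52–0.58 | 0.68–0.74 | 0.75–0.83 |
| 12 | 0.68–0.69 | 0.86 | 0.89–0.91 |

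A second set of simulations at mean 8 and +25% gave 0.46–0.51, 0.57–0.66 and 0.65–0.77. Taking both sets together gives 0.46–0.58, 0.57–0.74 and 0.65–0.83.

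In the tabulated settings about 41–46% of controls show some increase through counting noise alone, well above the planned 10%. Forcing about 10% versus 29% improvers required the control mean to fall by half; power was then 0.75, 0.91 and 0.998.

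**5. Counter-case.** Planned rates, 10% versus 30% improving, 62 per group, most children unchanged, increases and decreases of one strategy only.

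| Decliners in each arm | Chi-square | Wilcoxon on change | ANCOVA |
|---|---|---|---|
| 0% | 0.81 | 0.81 | 0.81 |
| 10% | 0.82 | 0.59 | 0.55 |
| 30% | 0.80 | 0.32 | 0.35 |

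With changes of up to three strategies and no decliners the values are 0.82, 0.81 and 0.75. Here the chi-square is as good or better.

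**6. No true effect.** Rejection rates in the simulations of step 4 were about 0.05–0.07 for all three methods.

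**The case against.** The strongest reply is that nothing here is inconsistent. Outcomes {12} specifies the percentage who improve, Sample size {14} is built on it, and the chi-square test matches both. This stands. It means that making the count primary changes the endpoint and does not merely analyse the same endpoint better.

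The second reply is that the size of the gain rests on inputs the protocol does not contain, and that the ordering reverses in the counter-case. This also stands, so no claim of higher power in every setting can be made. The counter-case does require most children to give exactly the same number of answers twice, about five days apart, in an open-ended task. That seems the less likely pattern, but the document cannot settle it.

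Third, Trial design {8} calls the framework exploratory, and p-values for secondary analyses are to be read descriptively. That lowers the urgency. It gives no reason to leave out a covariate that is already collected.

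A reader might also infer three stronger things:
- That the main test ignores baseline. It does not: the pre-test count is subtracted to define improvement.
- That the size of change is thrown away. The secondary Wilcoxon test uses it.
- That regression to the mean biases the result. Under randomisation it acts on both arms alike, and the simulated error rates show no material inflation. Chance imbalance costs precision only.

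**Conclusion.** The point holds as one of efficiency, not of error. The main test is valid, correctly sized for the assumed rates, and consistent with the stated outcome. If the game raises counts across the whole group, the yes/no cut costs roughly 38–55% of the sample's information under a normal change score, and adjustment for the pre-test value adds a further gain. At an assumed mean of 8 strategies and +25%, this is the difference between power of about 0.46–0.58 and 0.65–0.83. If the game only moves some children from no change to an increase, there is no gain and there may be a large loss.

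The part that does not depend on replacing the primary endpoint is the missing baseline adjustment in the analyses of the count, EROS and ESCQ. For these, a baseline-adjusted comparison is a near-free improvement on a test of change. The choice of primary endpoint is a trade-off for the investigators.

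**What to change.** 1. Replace the Wilcoxon tests on change for the strategy count, EROS and ESCQ with a comparison of the post-test value adjusted for the pre-test value, reported with a 95% confidence interval. ANCOVA suits the scales; ANCOVA or a count model suits the number of strategies.
2. Add the pre-test count to the independent variables of the logistic regression.
3. Trial status gives the trial as pre-recruitment. While that is so, consider making the adjusted count comparison primary and keeping the percentage improving as supportive. State the expected pattern of effect, since that decides which analysis is stronger.

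Items 1 and 2 need no new data, only protocol wording. Item 3 costs more: the registry entry must change, and Sample size {14} must be restated with a mean, variance and pre-post correlation that the protocol does not now give. The headline result would become a difference or ratio of counts instead of a percentage of improvers.
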